## Data collection and management

### Plans for assessment and collection of outcomes {18a} {18b(i)-p}

Demographic, physical, and laboratory outcome data will be collected via the EDC system. The questionnaires will be given to the participants in paper-booklet form to fill out by themselves at home or by each study institution before each outpatient clinic (at T1, T2, T3, and T4) to eliminate any observer bias. After the booklet is returned, a study investigator or a research assistant at each institution will check that the participant has answered all the questions and ask him/her to reply to any questions skipped. Then, these booklets will be sent to the data center in envelopes by the investigator.

### Plans to promote participant retention and complete follow-up {18b} {18b(ii)-p}

The attending physician plans the patients’ clinic appointments according to the time points of the outpatient clinic when the study participant will be assessed (at T2, T3, and T4). The data center will send an email reminder to each investigator before the time point of the outpatient clinic. If participants miss a scheduled follow-up appointment, the primary physician will try to call them to visit to the outpatient clinic. For patients who drop out from this study, data will be included as intention-to-treat.

### Data management {19}

Each patient will be coded with a research number via the EDC system at first enrollment, and their data will be collected via the EDC system. To improve the data quality, the EDC is designed to prevent the input of unrealistic values. Independent of statistical analysis by the statistician, all data will be checked before analysis by the data center.

### Confidentiality {27}

A research number will be assigned to each patient on first enrollment. This number will be used for data registration. After completion of this study, the raw data will be retained at each institution for 10 years following the publication of the first survey results.

### Plans for collection, laboratory evaluation, and storage of biological specimens for genetic or molecular analysis in this trial/future use {33}

This is not applicable because all biological samples were destroyed and no further analysis was performed after this study.

## Statistical methods

### Statistical methods for primary and secondary outcomes {20a}

#### Analysis of primary endpoint

For each group, point estimates and 95% confidence intervals (CIs) will be reported. We will use an independent *t* test to compare groups.

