### Trial design {8}

This study was designed as an open-label, multicenter, parallel-group, randomized controlled trial (RCT). Patients will be randomly allocated 1:1 into two groups to compare the efficacy of ONS with that of usual care. The study protocol follows the Standard Protocol Items: Recommendations for Interventional Trials Patient-Reported Outcome extension (SPIRIT-PRO [29]) checklist (Additional file 1) and the Template for Intervention Description and Replication (TIDieR) checklist and guide [30]. The description of interventions recommended by TIDieR can be found in Additional file 2. The flow diagram for recruitment and randomization is shown in Fig. 1.

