## Primary outcome measure

The %BWL from T1 to T2 after surgery will be the primary outcome in this study. To minimize the measurement bias between each time point, the same weight meter at each institution will be used under similar conditions, such as clothes and time after meal.

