### Sample size {14}

The results of previous studies [10, 43–46] showed that the estimated mean percentage of the BWL at 8 weeks after surgery for gastric cancer is approximately 8%, with a standard deviation of approximately 5.5%. We anticipate that this percentage might be reduced to 5% in the ONS group, with a mean difference of 3%. To detect this difference, this RCT will require 106 participants for a two-sided significance level of 0.05 and 80% statistical power. The estimated total sample size is approximately 120 (60 patients per group) considering patients probably lost to follow-up and dropouts of approximately 10% from the 1st to 2nd enrollments.

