## Assignment of interventions: allocation

### Sequence generation{16a}

Software developed by Zenbe Co., Ltd. and the stratified block method with permuted blocks will be used to perform the randomization under the supervision of the independent statistician (AN). The group sizes will be balanced according to clinical stage (I or ≥ II) and surgical procedure (TG or non-TG).

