#### Analysis of secondary endpoint {20a-p}

The analysis of secondary outcomes will be explanatory to complement the primary analyses, so no adjustments for multiplicity will be made for these outcomes. Point estimates and 95% CIs will be reported, and *p*-values will be calculated appropriately for continuous outcomes to compare groups.

We will use an independent *t* test for % BWL at T3 and T4. We will use a generalized linear mixed model with repeated measures analysis to estimate the mean difference in score changes from T1 to T2, T3, and T4 in the HRQoL of QLQ-C30, QLQ-OG25, and EQ-5D-5L between-group comparisons. Baseline values will be adjusted as fixed effects. We handled the timepoint as a categorical variable in the model. Missing values for some items in EORTC-C30 will be handled according to the recommendations in the EORTC QLQ-C30 scoring manual [47]. We will use an independent t test for the other secondary outcomes for each time point.

A significance threshold of *p* < 0.05 will be adopted for all tests. All statistical analyses will be performed with STATA software (StataCorp, LLC, College Station, Tex).

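### The primary t test leaves out the two factors used to stratify randomisation, so it is conservative to the extent that they predict weight loss, and it forgoes precision the design offers

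*Protocol article*

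**What the plan says.** **Randomisation.** Under Sequence generation, "the stratified block method with permuted blocks will be used to perform the randomization", and "The group sizes will be balanced according to clinical stage" and procedure (TG or non-TG). The Abstract names the same two factors. Under Trial design, "Patients will be randomly allocated 1:1 into two groups".

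**Primary outcome and test.** Under Primary outcome measure, "The %BWL from T1 to T2 after surgery will be the primary outcome in this study". T1 is before surgery and T2 is 8 weeks after. Under Analysis of primary endpoint, "We will use an independent *t* test to compare groups". No covariate or stratum is named.

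**Elsewhere in the plan.**
- A repeated-measures mixed model for %BWL appears under Sensitivity analyses, with no covariates stated.
- Procedure returns only as a subgroup. The stage subgroup uses pathological stage, whereas randomisation used clinical stage.
- Baseline adjustment ("Baseline values will be adjusted as fixed effects") is stated for the quality-of-life model.
- Under Sample size, "this RCT will require 106 participants for a two-sided significance level of 0.05 and 80% statistical power", for a difference of 3 points and an SD of about 5.5.

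**The concern.** Blocking within strata forces the arms to be nearly balanced on stage and procedure. If those factors affect weight loss, the balance removes their contribution from the true sampling variance of the difference between arms. An independent t test does not use this. It estimates its standard error from the whole within-arm spread, including the spread between strata, so the reported standard error exceeds the real one. The interval is then wider than it needs to be, and the test rejects less often than 5% under no effect.

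The stake is precision. The trial is sized for 80% power and recruitment has closed, so the analysis is the remaining place to gain information. Both factors are already recorded, because randomisation takes place 5 to 7 days after surgery, when stage group and procedure are known.

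**Working it through.** **1. Reproduce the plan's figure.** Inputs from Sample size: difference 3, SD 5.5, two-sided 0.05, power 80%, 1:1.

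n per arm = 2 × (5.5 × (1.960 + 0.842) / 3)² = 52.76, so 53 per arm and **106 in total**. This matches the article. (The noncentral t version gives 54 per arm.) The sample size therefore belongs to an unadjusted comparison with a marginal SD, and on those inputs the planned power is met.

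**2. Effect of adjustment in theory.** Let R² be the share of %BWL variance explained by stage and procedure. The article gives no value, so R² is an assumption throughout.

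- Residual SD = 5.5 × √(1 − R²)
- Adjusted SE at 53 per arm = residual SD × √(2/53)
- Narrowing of the interval = 1 − √(1 − R²)
- Size of the unadjusted test under perfect balance = 2 × [1 − Φ(1.96 / √(1 − R²))]

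| Assumed R² | SE | Interval narrower by | Size of t test |
|---|---|---|---|
| 0 | 1.068 | 0% | 5.0% |
| 0.05 | 1.041 | 2.5% | 4.4% |
| 0.10 | 1.014 | 5.1% | 3.9% |
| 0.20 | 0.956 | 10.6% | 2.8% |

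**3. Check by simulation.** 106 patients in four strata. Assumed: blocks of 4, half the patients in each stage group, 20% TG, R² split equally between the two factors. 10,000 runs per scenario. The adjusted model contains arm, stage and procedure. SEs and sizes come from the runs with no effect.

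| Assumed R² | Mean SE, t test | True SD of the t test's estimate | Size: t test / adjusted | Power at 3 points: t test / adjusted |
|---|---|---|---|---|
| 0 | 1.064 | 1.066 | 5.1% / 5.1% | 79.5% / 79.4% |
| 0.05 | 1.067 | 1.053 | 4.7% / 5.2% | 79.3% / 80.9% |
| 0.10 | 1.066 | 1.004 | 3.7% / 4.7% | 80.8% / 83.4% |
| 0.20 | 1.068 | 0.967 | 2.9% / 5.0% | 81.5% / 87.0% |

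As R² rises, the t test's reported SE stays near 1.07 while the true SD of its estimate falls. The power gain from adjustment is 1.6, 2.6 and 5.5 points at R² of 0.05, 0.10 and 0.20.

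**4. What R² might be.** For procedure alone, R² = q(1 − q)D² / 5.5², where q is the TG share and D the difference in %BWL between TG and non-TG patients. Both are assumed.

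- q = 0.20 and D = 3: 0.16 × 9 / 30.25 = 0.05
- q = 0.20 and D = 4: 0.16 × 16 / 30.25 = 0.08
- q = 0.20 and D = 5: 0.16 × 25 / 30.25 = 0.13
- q = 0.30 and D = 6: 0.21 × 36 / 30.25 = 0.25
- q = 0.15 and D = 2: 0.1275 × 4 / 30.25 = 0.02

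**The case against.** The best defence is that design and test agree with each other. The sample size was set for an unadjusted comparison, the point estimate is not biased by leaving the factors out, and any error in size lies below 5%. All of that stands, and it limits the point to forgone precision.

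It could also be said that a fuller analysis plan may bring in the factors. But the article does not leave the primary test open. It names one, and nothing in it adds the strata.

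Several stronger readings are tempting, and the article does not support them.

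- **The trial loses planned power.** It does not. In simulation the t test stays between 79.3% and 81.5% across the R² values tried.
- **The standard error is wrong as a matter of fact.** It is too large only if the factors predict %BWL. The article names them without giving a reason, so that they were chosen as predictors of weight loss is an inference. Stratifying on procedure and planning a subgroup by it make the inference plausible but do not prove it.
- **Baseline weight is wrongly ignored, given that quality of life gets baseline adjustment.** %BWL is already expressed relative to T1 weight, and weight is not a stratification factor. Omitting it does not make the standard error wrong for this design.
- **No interval for the between-group difference is planned.** The primary section mentions intervals for each group and then a comparison. It does not exclude an interval for the difference, and that detail can sit in an analysis plan.

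A practical objection also stands. Changing a primary test after recruitment has closed, in an open-label trial whose statisticians know the allocation, can look data-driven. It affects how and when the change is made.

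**Conclusion.** The point holds in a limited form. The primary test does not match the randomisation, and the consequence is conservative. Under assumed R² of 0.05 to 0.20, the simulated size is about 4.7% to 2.9% instead of 5%, adjustment would add about 2 to 6 power points, and the interval would narrow by about 2.5% to 11%. With R² near 0 there is no loss. These sizes rest on the assumed R² and, for the simulated figures, on the assumed block size and stratum shares. The direction of the error rests only on the stratified design and on the factors being prognostic. False positives are not inflated. This is a worthwhile improvement at little cost and does not threaten the trial's validity.

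**What to change.** Make the primary analysis a linear model of %BWL at T2 on arm, clinical stage (I or ≥ II) and procedure (TG or non-TG), with the strata as recorded at randomisation. Report the adjusted between-group difference with its 95% confidence interval as the primary result, and keep the independent t test as supportive. Put the same two factors in the mixed-model sensitivity analysis of %BWL. Baseline weight or BMI may be added if prespecified, but that is optional and not part of the error.

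Timing matters. The Blinding section says statisticians know the allocation, and Trial status says recruitment ended on 5 January 2024. The change should be dated and documented before any outcome is compared by arm. If that comparison has already been made, leave the t test as primary and report the adjusted model as a labelled supportive analysis.

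The cost is a short change to the analysis text and code, plus the ethics approval that Protocol amendments requires. No new data are needed.

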#### Analysis of secondary endpoint {20a-p}

The analysis of secondary outcomes will be explanatory to complement the primary analyses, so no adjustments for multiplicity will be made for these outcomes. Point estimates and 95% CIs will be reported, and *p*-values will be calculated appropriately for continuous outcomes to compare groups.

We will use an independent *t* test for % BWL at T3 and T4. We will use a generalized linear mixed model with repeated measures analysis to estimate the mean difference in score changes from T1 to T2, T3, and T4 in the HRQoL of QLQ-C30, QLQ-OG25, and EQ-5D-5L between-group comparisons. Baseline values will be adjusted as fixed effects. We handled the timepoint as a categorical variable in the model. Missing values for some items in EORTC-C30 will be handled according to the recommendations in the EORTC QLQ-C30 scoring manual [47]. We will use an independent t test for the other secondary outcomes for each time point.

A significance threshold of *p* < 0.05 will be adopted for all tests. All statistical analyses will be performed with STATA software (StataCorp, LLC, College Station, Tex).

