### Outcomes {12}

Evaluations will be performed before surgery (T1) and at 8 weeks (T2), 6 months (T3), and 12 months after surgery (T4). Baseline measurements (T1) of laboratory data are to be collected within 45 days prior to surgery, and the other outcome measures including body weight, handgrip strength and HRQoL are to be collected within 14 days prior to surgery. In particular, body weight will be required to be measured at a time as close to the date of surgery as possible at T1 and will be measured at T2 to T4 using the same weight scale and with patients in light clothing as at T1.

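### Handgrip, laboratory values and dietary intake are compared by separate unadjusted t tests, although baselines are collected and HRQoL already gets a baseline-adjusted repeated-measures model

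*Protocol article*

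**What the plan says.** Under Analysis of secondary endpoint {20a-p}, the protocol article sets three different analyses.

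- Later weight loss: "We will use an independent *t* test for % BWL at T3 and T4".
- HRQoL: a repeated-measures mixed model for score changes at T2, T3 and T4, with visit as a category. "Baseline values will be adjusted as fixed effects".
- Everything else continuous: "We will use an independent t test for the other secondary outcomes for each time point". No covariate is named.

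The list of secondary outcome measures shows what falls under the last rule. Handgrip is a change from T1 to T2, T3 and T4. The three laboratory measures are listed at T2, T3 and T4. Dietary caloric intake is listed at T1 and T2 and is collected at 14 institutions.

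Baselines exist for all of them. For the blood measures, Outcomes {12} says: "Baseline measurements (T1) of laboratory data are to be collected within 45 days prior to surgery". The same section sets a shorter preoperative window of 14 days for weight, grip and questionnaires. Dietary intake at T1 is in the outcome list itself.

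The Sensitivity analyses section adds a repeated-measures mixed model for change in %BWL. It does not mention baseline adjustment. It plans nothing similar for handgrip, laboratory values or diet.

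**The concern.** The section treats outcomes measured on the same patients at the same visits in two ways and gives no reason. HRQoL uses the baseline and all follow-up visits together. Handgrip and the laboratory values are cut into separate two-sample comparisons without a baseline covariate.

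Three things are lost:

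- Precision, because variation between patients that T1 would explain stays in the error term.
- Protection against chance imbalance. In a trial of about 120 patients the arms can differ at T1 in albumin or grip by luck, and an unadjusted comparison carries part of that difference into the estimate.
- Information from patients who miss a visit. A t test at T3 or T4 drops them. A mixed model can still use their other visits.

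Muscle strength is one of the trial's three stated aims, so a clear answer on handgrip matters more than for a routine secondary outcome.

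**Working it through.** **The plan's own figure.** Sample size {14} gives a difference of 3 points, SD 5.5, two-sided alpha 0.05 and 80% power. Per arm, n = 2(1.96 + 0.8416)² × 5.5² / 3² = 52.8, rounded up to 53, so 106 in total. This matches the stated 106. Dropout of 10% gives 106 / 0.90 = 118, or approximately 120. That figure rests on the primary endpoint and does not change with anything below.

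**Inputs.** Assume equal variance at T1 and follow-up (set to 1) and correlation r between them. The documents state no r, so a range is shown. The variance of the group difference is then proportional to:

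- level at follow-up: 1
- change from baseline: 2(1 − r)
- adjusted for baseline (ANCOVA): 1 − r²

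The SE ratio of ANCOVA is √(1 − r²) against levels, and √[(1 − r²) / (2(1 − r))] = √[(1 + r) / 2] against change.

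| r | SE ratio vs level | reduction | SE ratio vs change | reduction |
|---|---|---|---|---|
| 0.3 | 0.954 | 5% | 0.806 | 19% |
| 0.5 | 0.866 | 13% | 0.866 | 13% |
| 0.7 | 0.714 | 29% | 0.922 | 8% |
| 0.8 | 0.600 | 40% | 0.949 | 5% |

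At r = 0.5, 106 × 0.75 = 79.5, so about 80 adjusted patients give the precision of 106 unadjusted ones under either comparison.

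**Illustrative power.** For a difference of 0.5 SD with 53 per arm, power = Φ(0.5 / √(2v/53) − 1.96), where v is the variance factor above:

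| r | level | change | ANCOVA |
|---|---|---|---|
| 0.3 | 73% | 59% | 77% |
| 0.5 | 73% | 73% | 84% |
| 0.7 | 73% | 91% | 95% |

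**Chance imbalance.** With 53 per arm, the SE of the T1 difference is √(2/53) = 0.194 SD. Given a T1 difference D, a comparison of levels is shifted by rD and a comparison of changes by −(1 − r)D. For D of one SE:

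- r = 0.3: levels 0.3 × 0.194 = 0.06 SD; changes 0.7 × 0.194 = 0.14 SD the other way.
- r = 0.5: 0.10 SD for each, in opposite directions.
- r = 0.8: levels 0.8 × 0.194 = 0.16 SD; changes 0.2 × 0.194 = 0.04 SD the other way.

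Baseline adjustment removes this shift in expectation.

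**Which column applies.** Handgrip is defined as a change, so the change column applies. The laboratory values are listed as levels, and intake is listed by time point, so the level column applies on that wording. No gain is computed for %BWL, because it is already a percentage of T1 weight.

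**The case against.** The strongest reply is that nothing here is an error. An independent t test between randomised arms is valid, it matches the primary analysis, and the section presents the secondary analyses as complementary and without multiplicity control. That stands: the point is about efficiency and consistency. A reader who infers that the t tests are biased by design goes further than the documents allow.

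Other parts of the reply also stand:

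- **Handgrip.** A reader might infer that muscle strength gets the least efficient analysis. Its baseline already enters through the change score, which is more precise than a level once r exceeds 0.5. At r = 0.8 the remaining gain is about 5%. The 40% figure does not apply to handgrip.
- **Laboratory values.** The list uses the same wording for HRQoL, yet HRQoL is analysed as change. If the laboratory values are also to be analysed as changes, the change column applies to them. The article does not settle this.
- **The size of r.** High correlations are not assured. Laboratory T1 may be 45 days before surgery, gastrectomy lies between T1 and every later visit, and some patients start adjuvant chemotherapy. Quoting only the gain at high r would overstate the point.
- **Missing visits.** A reader might infer that the t tests require data missing completely at random. That is too strong: missingness may differ between arms if it is unrelated to outcome within each arm. The article gives no loss figure for T3 or T4.
- **%BWL.** It already embeds baseline weight and has a mixed model as a sensitivity analysis, so it is not left unhandled. Nor can that model be cited as baseline-adjusted, since the article does not say so.

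What the reply does not answer is why a covariate already in hand is used for HRQoL and not for handgrip, laboratory values or diet. The test for these is stated outright, so this is not a detail left to an analysis plan.

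**Conclusion.** The point holds as a matter of precision and consistency. Handgrip change, laboratory values and dietary intake are compared by unadjusted t tests although T1 is available and the same section has a better model. Under equal variances, baseline adjustment is at least as precise as either t test at every r considered. Its gain runs from about 5% to 40% of the SE against levels and from about 19% down to 5% against change as r goes from 0.3 to 0.8. These sizes depend on an assumed r.

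For dietary intake only the missing baseline adjustment matters, since there is one follow-up visit. For %BWL at T3 and T4 the gain is mainly in the handling of missed visits. These are secondary outcomes without multiplicity control, so the weight is moderate. Neither the primary analysis nor the 106 is affected.

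**What to change.** In a dated amendment before analysis:

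- **Handgrip and laboratory values at T2 to T4:** use the mixed model already given for HRQoL. Write out its terms: the outcome's T1 value, visit as a category, arm, arm by visit, and the two stratification factors (clinical stage and TG or non-TG). Report the adjusted difference at each visit with its 95% CI.
- **Dietary intake at T2:** ANCOVA on T1 intake with the same stratification factors, in the patients from the 14 institutions.
- **%BWL at T3 and T4:** report the mixed model from the Sensitivity analyses section for these visits too, with the stratification factors added.
- **The existing t tests:** keep them as supportive, and state whether the laboratory values and intake are compared as levels or changes.

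No new data and no change of sample size are needed. The cost is more than a change of wording. Trial status reports recruitment finished on 5 January 2024, and under Who will be blinded {17a} the statisticians know the allocation. The amendment must therefore be dated and justified before outcomes are compared by arm. If that comparison has already been made, the adjusted analyses should be labelled as added afterwards.
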